### Participants

#### Study cohort

All men newly diagnosed with prostate cancer in Queensland between 1st February 2005 and 31st July 2007 were potentially eligible for the study. Urologists referred eligible men to the study if they were newly diagnosed with prostate cancer irrespective of stage of disease. The following exclusion criteria were used: previous diagnosis of prostate cancer; inability to read, write and speak English; history of dementia, head injury or psychiatric illness; and no regular access to a telephone.

In all, 1291 men were referred to the study, with 1064 men (82.4% of referrals) eligible and agreeing to participate. Figure 1 shows the flowchart of ineligible/excluded men, completeness of data collection and attrition from the study between recruitment and 12 months post-treatment.

**Figure 1 F1:**
[figure not shown]
**Flowchart of recruitment, participation, data collection and attrition from study**.

#### Population cohort

Clinical and diagnostic information for *all *men diagnosed with prostate cancer in Queensland during the study period (February 2005 to July 2007), whether or not they are in the study cohort, was accessed via the Queensland Cancer Registry. This population-based data will enable a comparison of demographic, geographical, clinical and diagnostic information between the study cohort and men diagnosed with prostate cancer who did not take part in the study (n = 5545).

### Individual-level data

#### Telephone and self-administered questionnaires

Data collection for the study cohort is via telephone and self-administered questionnaires and occurs at pre-treatment and 2 months, 6 months, 12 months, 24 months, 36 months, 48 months and 60 months post-treatment. These assessments include demographic information, medical history, self-reported diagnostic and treatment information together with outcomes associated with prostate cancer, including information about quality of life and psychological adjustment. The quality of life and psychological measures used in this study are well-established and validated and have been described previously[19].

##### Demographics

the demographic information collected at baseline includes date of birth, marital status, ethnicity, education level, income, current employment status and health insurance.

##### Medical history

includes family history of cancer, family history of prostate cancer, body mass index (BMI), other chronic conditions and co-morbidities and smoking status.

##### Self-reported diagnostic and treatment information

This self-reported information includes PSA level, Gleason score, previous screening history, the diagnostic examinations performed together with the date and location of each examination, the reasons leading to the initial diagnosis, reasons for delaying the diagnosis, the type of treatment undertaken and the date and location of each type of treatment and the public or private status of the treating facility. Detailed self-report diagnostic and treatment information is collected on all participants up to 6 months after primary treatment commenced. We will continue to collect basic information on disease progression and subsequent treatments up to 60 months following primary treatment.

#### Medical Records

For the study cohort, detailed treatment information is being abstracted from participants' medical records held in hospitals and private treatment facilities. This includes details of diagnosis and post-treatment PSA levels, TNM Staging, diagnostic examinations performed and the dates and locations of these examinations, the types of treatment and the treating doctors and their facilities. Any information pertaining to further treatments such as radiation therapy, androgen deprivation therapy and other medications is being collected as relevant. Detailed information from medical records is collected from diagnosis to 12 months after primary treatment was started.

#### Medicare Information

Study participants are being asked to sign an additional consent form to facilitate access to their medical records through Medicare Australia. Data relating to health service utilisation including general practitioner and specialist services, prescription drug use (from the Pharmaceutical Benefits Scheme), diagnostic and imaging tests and procedures is being obtained. Information requested from Medicare Australia will cover a 7 year period starting from the 1^st ^January 2005 for each study participant.

#### Queensland Cancer Registry data collection

For the entire population cohort, information is obtained from the Queensland Cancer Registry (QCR) regarding the clinical details recorded for each prostate cancer diagnosis. These details include the Gleason score, the tumour volume, number of positive cores, the extent of invasion (including extraprostatic extension, seminal vesicle invasion and vascular invasion), and, when radical prostatectomy is performed and a lymhadenectomy is also undertaken, the number of positive lymph nodes. When available and relevant, details are obtained from multiple pathology reports sourced within the Queensland Cancer Registry including transrectal ultrasound (TRUS), Transurethral Resection of the Prostate (TURP), prostatectomy, lymph node dissection and bone biopsy pathology reports.

Information will also be gathered from the QCR on date of diagnosis, place of usual residence at diagnosis, age group at diagnosis, gender, country of birth, marital status, occupation and Indigenous status. Although there is evidence of some under-identification, the Indigenous identifier in Queensland is considered to have good coverage [21].

### Area-level information

The smallest geographical entity used for this analysis is Collection Districts (CDs) which cover Queensland without gaps or overlap. There were 7567 populated CDs in Queensland in 2006, with a median population of 497 (range: 3 to 2372). These CDs can then be collapsed to form Statistical Local Areas (SLA) using a deterministic (m:1) match between the CDs and the SLAs.

These SLAs are often based on local government administrative areas, with the local governments being responsible for local and regional service provision and infrastructure. In 2006 there were 478 SLAs in Queensland with a median population of 5810 (range: 7 to 77523). The SLA is also used as the standard geographical area definition by most relevant data providers, in particular the Queensland Cancer Registry and Australian Bureau of Statistics. The use of geo-coding enables us to match all area-level information to the 2006 Australian Standard Geographic Classification definition, thus removing any impact of changes in these geographic boundaries over time.

#### Remoteness

Remoteness of residence when diagnosed with breast cancer was categorized using the ARIA+ classification [22], which categorizes remoteness into Major City, Inner Regional, Outer Regional, Remote and Very Remote areas. The ARIA+ classification is a purely geographic measure that considers road distance measurements from localities, and is a measure of accessibility and remoteness.

#### Socioeconomic status

Area-level socioeconomic disadvantage is measured using the Index of Relative Socioeconomic Disadvantage (IRSD) calculated by the Australian Bureau of Statistics [23]. The IRSD provides a general measure of disadvantage, and considers factors such as low income, low educational attainment, high unemployment, jobs in relatively unskilled occupations.

#### Census data

The Australian Bureau of Statistics conducts a population Census every 5 years, with the latest available data currently available for 2006. Information is available down to CD level, and then can be aggregated up to SLA level. Variables include occupation, household income, number of vehicles per occupied private dwelling, marital status, Indigenous status, labour force status and highest educational qualification.

Details about occupation were collapsed into "Blue Collar" (including tradespersons, plant and machine operators and drivers, and labourers and related workers), "White collar" (including clerks, salespersons and personal service workers), "Professional" (including managers and administrators, professionals and para-professional), "Not in workforce" (including retired, students, unemployed and home duties), "Unknown" (no information available). Similar occupation categories have been used previously [24].

##### Geocoding of street address information

All address details for study respondents, diagnosing and treating doctors and treatment facilities are geo-coded using commercial software designed to clean and convert street address information into spatial (latitude and longitude) coordinates. When full street address information for a patient, doctor or treating facilities is not available, the centroid of the SLA will be used instead.

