##### Road travel distance calculations

Distances between patients, diagnostic centres, treatment facilities and other medical centres will be calculated directly from the geo-coded latitude and longitude points. Many studies assessing distance to treatment have calculated straight line distances [25-31], however this method may under-estimate travel times [29], illustrating the importance of using accurate road distance and travel time information [25,27]. These road distances and times will be calculated using commercial GIS software, combined with street network analysis and display tools: and custom GIS applications to enable calculation of the closest road travel distance between one location (such as patient's residence) and multiple locations (such as various treatment facilities).

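### Missing addresses of men, doctors and facilities are all placed at the SLA centroid, a coarse rule feeding the travel distances when a better one is available at little cost

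*Protocol article*

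**What the plan says.** Under Geocoding of street address information, addresses of respondents, doctors and facilities are converted to coordinates. For incomplete addresses the rule is: "When full street address information for a patient, doctor or treating facilities is not available, the centroid of the SLA will be used instead". No other fallback is named.

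The next section, Road travel distance calculations, says that distances "will be calculated directly from the geo-coded latitude and longitude points". It prefers road distances to straight lines, "illustrating the importance of using accurate road distance and travel time information".

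Under Area-level information, the CD is the finest unit: "The smallest geographical entity used for this analysis is Collection Districts (CDs) which cover Queensland without gaps or overlap". CDs map many-to-one to SLAs, and numbers and populations are given for both levels, but no land areas. The Census data section adds: "Information is available down to CD level, and then can be aggregated up to SLA level".

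**The concern.** One coarse point stands in for three kinds of location. In a large, thinly settled SLA the geometric centre may be far from the towns. This has three consequences:

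- **Men.** All centroid-located men in an SLA receive the same distance to a given facility. The model-building plan lists access to care among the individual-level factors. If travel distance serves as that factor, it varies only by area for these men, in a study meant to separate individual from area effects.
- **Facilities and doctors.** An error in a facility's position passes to every man linked to it.
- **Nearest facility.** The plan also looks for the closest of several facilities. A misplaced point can change which one is closest, as well as the number of kilometres.

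What is at stake is the accuracy of the travel-distance variable and of any association estimated from it.

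**Working it through.** The article states no figure for geocoding success, SLA area or distance error, so there is no figure of its own to reproduce.

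**1. What a weighted point needs.** Inputs from Area-level information: 7567 populated CDs and 478 SLAs.

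7567 / 478 = 15.8 CDs per SLA on average.

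An SLA point weighted by CD population uses only CD positions and population counts. It does not require knowing which CD a man lives in.

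**2. Positional error of a geometric centroid (illustration).** Treat the SLA as a disc of area A with residences spread evenly. The mean distance from residence to centre is (2/3) × √(A/π) = 0.376 × √A. For a square the coefficient is 0.383, so shape matters little. The areas below are assumptions:

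| Assumed SLA area (km²) | 0.376 × √A (km) |
|---|---|
| 10 | 1.2 |
| 500 | 8.4 |
| 5,000 | 26.6 |
| 50,000 | 84 |

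If residents instead cluster in one town away from the centre, all affected men in that SLA carry the same error, and it does not average out.

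**3. Error in distance to a facility (illustration).** For a facility at distance D, well outside a disc of radius R = √(A/π), the mean absolute straight-line error is close to 4R/(3π). A simulation agreed. Both A and D are assumed:

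| A (km²) | D (km) | R (km) | Mean absolute error (km) | Error / D |
|---|---|---|---|---|
| 10 | 10 | 1.8 | 0.8 | 8% |
| 500 | 50 | 12.6 | 5.4 | 11% |
| 5,000 | 200 | 39.9 | 16.9 | 8% |
| 50,000 | 600 | 126.2 | 53.5 | 9% |

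Absolute error rises with area. Under these pairs relative error does not.

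**4. How many men share an SLA.** The Power calculations section reports 270 SLAs with 1 to 66 respondents each (mean 3.9, median 2; 1064 / 270 = 3.9). Sharing one imputed distance is therefore possible in many SLAs, but the groups would usually be small. How many of these men lack a full address is not given, so the number affected cannot be computed.

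**The case against.** The strongest reply is that this is a rarely used fallback in a condensed article. Respondents are consenting men contacted repeatedly, treatment locations come from the men and their records, and the recruiting hospitals are named. Few addresses may be missing, and no facility is shown to lack one. The primary outcomes are pathways, intervals and treatment details, not distance. These points stand, and they keep the matter small. They do not make the centroid a better rule when it is used.

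A second reply is that the accuracy remark contrasts road with straight-line distance and sets no standard for address precision. That is fair: the two sections do not contradict each other. A third is that snapping to roads is normally part of network routing, so a centroid off the road network is a weak worry. That also stands.

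A fourth is that the centroid may already be population-weighted. The text does not say so, and the unqualified term ordinarily means the geometric centre. If weighting is intended, one word would settle it.

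Three stronger readings are tempting but unsupported:

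- **That finer locations are already held for the affected records.** CD-level Census data describe areas. Placing a man in a CD normally needs the address that is missing, and no CD, locality or postcode is said to be known for these records. The registry itself works at SLA level: "The SLA is also used as the standard geographical area definition by most relevant data providers, in particular the Queensland Cancer Registry".
- **That remoteness is distorted.** It comes from ARIA+, which is not shown to use these points.
- **That remote men carry the worst errors.** This needs remote SLAs to be larger in land area, which is plausible but not stated, and it concerns absolute error only.

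**Conclusion.** The point holds as a minor improvement. The article fixes a single coarse location rule for patients, doctors and facilities and calculates distances directly from the result. On the plain reading of centroid, the absolute positional error grows with SLA area, centroid-located men in an SLA share one distance to a given facility, and any facility error is passed on to all linked men.

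The actual size is unknown. The kilometre figures rest on assumed SLA areas, facility distances and evenly spread residences, and only show the possible range. The effect is confined to travel-distance variables and the analyses that use them. Nothing shows that the comparisons by ARIA+ remoteness category would change.

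**What to change.** - For a man without a full street address, use the finest locality known for that record. Failing that, use an SLA point weighted by CD population from the available Census counts.
- Locate named facilities and doctors' practices individually, not by SLA centroid.
- Flag every imputed point and report the share of imputed records by remoteness category.
- Repeat the distance analyses without the imputed points.

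The cost is a little more geocoding work and one further set of distance analyses. No new contact with the men is needed.

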##### Road travel distance calculations

Distances between patients, diagnostic centres, treatment facilities and other medical centres will be calculated directly from the geo-coded latitude and longitude points. Many studies assessing distance to treatment have calculated straight line distances [25-31], however this method may under-estimate travel times [29], illustrating the importance of using accurate road distance and travel time information [25,27]. These road distances and times will be calculated using commercial GIS software, combined with street network analysis and display tools: and custom GIS applications to enable calculation of the closest road travel distance between one location (such as patient's residence) and multiple locations (such as various treatment facilities).

##### Primary Outcome Measures

Diagnostic pathway: a description of events and time line from first noticing symptoms or presenting to a medical practitioner to the definitive diagnosis. This includes the diagnostic interval, defined as the time between the initial doctor's consultation for reasons that led to the prostate cancer diagnosis, and the date of definitive diagnosis.

Treatment pathway: a description of events and time line from the definitive diagnosis to 6 months post the commencement of primary treatment. This includes the treatment interval, which is the time between the definitive diagnosis and the commencement of primary treatment for the prostate cancer.

Treatment details: a description of the type, duration and frequency of all treatments received by the participant between diagnosis and 6 months after the commencement of primary treatment. Primary treatment is considered the first most invasive treatment undergone by the participant and is generally radical prostatectomy or radiation therapy (either external beam radiotherapy or brachytherapy). For participants who chose watchful waiting or active surveillance, date of treatment is considered as the date the treatment decision is made.

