For localised prostate cancer, potentially curative treatment options include surgery through radical prostatectomy and radiation therapy (external beam and brachytherapy). While these surgical or radiation treatments may increase the chance of cure, they are associated with a significant risk of impotence, and less commonly urinary incontinence and bowel problems. The prevalence and type of side-effects vary for different treatment types[10]. Another treatment option is active surveillance, in which treatment is initially deferred, then initiated if the disease progresses. This differs from "watchful waiting" in which medical treatment is reserved until symptoms become evident, thus potentially missing the opportunity for cure. In contrast close observation maintains the likelihood of cure by intervening before symptoms present.

The contrasting initial results recently published from two large-scale prostate cancer screening trials in the United States [11] and Europe [12] highlight the complexity of issues surrounding the provision of diagnostic and treatment services for prostate cancer. In the presence of already high PSA testing, the United States study suggested that organised PSA population screening programs are likely to result in over-diagnosis and over-treatment with little reduction in mortality. Conversely, in Europe where the prevalence of asymptomatic detection is low, there is greater potential for screening programs to reduce the number of advanced prostate cancers and deaths from prostate cancer. A sub-study conducted in Göteborg, Sweden, a country with a low prevalence of PSA testing (3%)[13] found that using an intention to treat analysis PSA testing almost halved the risk of death from prostate cancer. A major difference between this study and its two larger international predecessors is its more appropriate duration of follow-up viz. 14 years.

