### Statistical analysis

Statistical analyses for this study will reflect the sampling design, the data collection process, and the research objectives as stated previously. Due to the typically highly skewed distributions of time to diagnosis or treatment, standard methods for transforming the time intervals such as the geometric mean or comparing median times, will be used in the analyses. Crude and adjusted logistic and multinomial regression analyses of dichotomous and ordinal outcomes respectively, will be used to assess the contribution that independent factors have on men's choice of treatment. We will also investigate the representativeness of the study cohort compared to the rest of the men diagnosed with prostate cancer by comparing the distributions of those clinical and demographic variables collected from the Queensland Cancer Registry.

Previous studies looking at patterns of diagnosis and treatment have focussed on the individual-level data, or ecological studies. In order to appropriately investigate whether the observed patterns are due to the characteristics of the cancer patients themselves, or the characteristics of the geographical areas in which the individuals live, it is important to be able to quantify the variation between areas in terms of their diagnostic and treatment profiles. Thus using a multilevel analytical design we can then determine whether the observed variation is due to the clustering of individuals (i.e. a composition effect) or the environmental characteristics of the areas (i.e. a context effect).

We have previously described the advantages of incorporating a multilevel perspective [32]. We will use multilevel models to assess whether geographic remoteness and area-level disadvantage were associated with prostate cancer outcomes after controlling for individual-level socio-demographic characteristics. These models will be fitted using MLwiN version 2.15 (University of Bristol, United Kingdom).

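### The treatment interval stops at the decision for men on watchful waiting or active surveillance but at treatment start for other men, so pooled comparisons mix two quantities

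*Protocol article*

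**What the plan says.** In the protocol article, Primary Outcome Measures, the treatment pathway contains the treatment interval, "which is the time between the definitive diagnosis and the commencement of primary treatment for the prostate cancer". Under the treatment-details measure, the same section says which treatment counts: "Primary treatment is considered the first most invasive treatment undergone by the participant and is generally radical prostatectomy or radiation therapy". It then sets a separate date for men not treated at once: "For participants who chose watchful waiting or active surveillance, date of treatment is considered as the date the treatment decision is made".

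Recruitment does not limit the cohort to one kind of management: "Urologists referred eligible men to the study if they were newly diagnosed with prostate cancer irrespective of stage of disease". For the time intervals, the Statistical analysis section says that "standard methods for transforming the time intervals such as the geometric mean or comparing median times, will be used in the analyses". The individual-level factors listed for the second stage of the multilevel models are patient characteristics, disease stage, co-morbidity and access to care; type of management is not named. No section limits the interval to actively treated men or reports it separately by management.

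**The concern.** For a treated man the interval has two parts: diagnosis to decision, and decision to start of treatment. The second part is where waiting lists, travel and availability of services act. For a man on surveillance only the first part is counted. When the two kinds of interval are pooled, a group with more surveillance has a shorter average interval even if every man in both groups decides and is served at the same speed.

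Study Aims, item 2, asks for the determinants of area-level and individual-level variation in treatment pathways. In the multilevel models, a difference in management mix would first appear as variation between areas. Whatever the individual-level covariates did not absorb could then be read as an effect of remoteness or disadvantage. The Background cites lower radical prostatectomy rates in rural and regional Australia, so a difference in mix along the remoteness scale is plausible.

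A smaller problem lies in the wording on primary treatment. "Primary treatment is considered the first most invasive treatment undergone by the participant" can be read as dating a man at a later, more invasive therapy when another treatment had already begun. It also does not say how it ranks against the decision-date rule for a man on "active surveillance, in which treatment is initially deferred, then initiated if the disease progresses".

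**Working it through.** The article gives no figure for the treatment interval, the surveillance share or the lag from decision to treatment, so there is no stated result to reproduce. The definitions are compared first. The size is then illustrated with assumed values.

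**Definitions side by side.** Let D be the time from diagnosis to decision and L the time from decision to start of treatment.

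- Active treatment: interval = D + L.
- Watchful waiting or active surveillance: interval = D.

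The decision-date sentence stands under treatment details and speaks of the date of treatment, whereas the interval refers to commencement of primary treatment. Applying the sentence to the interval is the natural reading, because these men otherwise have no end date.

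**Closed-form illustration.** Assumptions: geometric mean time to active treatment t = 80 days, geometric mean time to decision for surveillance men d = 30 days, both the same in every area. With surveillance share s, the pooled geometric mean is exp[(1 − s) ln t + s ln d].

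- s = 0.10: exp(0.90 × 4.382 + 0.10 × 3.401) = exp(4.284) = 72.5 days.
- s = 0.25: exp(0.75 × 4.382 + 0.25 × 3.401) = exp(4.137) = 62.6 days.
- Ratio: (30/80)^(0.25 − 0.10) = 0.375^0.15 = 0.863, that is 13.7% shorter.

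The ratio is (d/t)^(difference in share), so it depends only on d/t and on the gap between the two shares.

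| Varied assumption | Ratio | Change |
|---|---|---|
| d = 40, shares 20% v 10%, t = 80 | 0.50^0.10 = 0.933 | −6.7% |
| d = 20, shares 30% v 10%, t = 80 | 0.25^0.20 = 0.758 | −24.2% |
| t = 60, d = 30, shares 25% v 10% | 0.50^0.15 = 0.901 | −9.9% |
| t = 120, d = 30, shares 25% v 10% | 0.25^0.15 = 0.812 | −18.8% |
| shares reversed (10% v 25%), t = 80, d = 30 | 1/0.863 = 1.158 | +15.8% |
| equal shares | 1 | 0 |

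**Simulation with the same D in everyone.** D is lognormal with median 30 days and log-SD 0.7 in all groups. L is lognormal with log-SD 0.7 and median 14, 30 or 60 days.

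| Median L | Median interval, surveillance | Median interval, active treatment | Geometric mean ratio, 30% v 10% surveillance | Median difference, 30% v 10% |
|---|---|---|---|---|
| 14 days | 30.0 | 48.3 | 0.91 | −3.4 days |
| 30 days | 30.0 | 66.9 | 0.85 | −7.7 days |
| 60 days | 30.0 | 98.8 | 0.79 | −14.9 days |

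By construction time to decision does not differ, and L is the same for all treated men. The gap between management types (about 18, 37 and 69 days) therefore comes only from where the clock stops. The gap between area groups comes only from the share of men in each type.

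**The case against.** The convention is stated openly and gives an end date to men who would otherwise have none. Treatment type is recorded, so the analysts could split the interval without changing its definition, and a condensed article may leave that to an analysis plan. It is true that a date set by convention is acceptable in itself. But the article does more than omit a detail: it writes two end-points into one primary outcome and plans pooled summaries of it. Followed as written, those summaries mix the two quantities.

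Four stronger conclusions that a reader might draw are not supported:

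- **That surveillance is known to vary by area.** The Background reports radical prostatectomy rates only. A lower rate could be offset by radiation or other treatment, with no difference in surveillance.
- **That the main equity contrast is biased.** No such contrast is designated. The interval is one component of one of three descriptive primary outcome measures, and the power calculations concern proportions.
- **That later conversion from surveillance makes an area look slower.** The specific sentence covers men who chose surveillance and most naturally leaves them at their decision date. The self-report section also separates primary from subsequent treatments. What remains is an unclear order of precedence with the most-invasive-treatment wording, not a demonstrated second bias.
- **That time to decision can be computed for all men from data in hand.** The self-report section lists the date of each type of treatment. No section lists a decision date for actively treated men; one is implied only for surveillance men.

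**Conclusion.** The point stands in limited form. The treatment interval pools time to decision with time to decision plus the wait for treatment. A comparison between management types is distorted by definition. A comparison by area or socioeconomic status is distorted only to the extent that the surveillance share differs between the groups, and not at all if shares and times are equal.

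Under the assumed 80 and 30 days and shares of 10% and 25%, the artefact is about 14% of the geometric mean. It runs from about 7% to 24% when the higher share is 20% to 30% and the decision time 20 to 40 days. These are illustrations: every input is an assumption, and neither size nor direction in this cohort can be derived from the article. The possible misdating of men who had another therapy before the more invasive one is an ambiguity of wording, with no size attached.

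**What to change.** 1. Analyse diagnosis to treatment start only among men whose initial management is active treatment.
2. Report diagnosis to decision separately for men who chose watchful waiting or active surveillance. Extend it to all men only if a decision date was recorded for treated men. Recruitment ended in July 2007, so a date not recorded then may not be recoverable.
3. State that, for dating the interval, a man who chose surveillance keeps his decision date if he later escalates, the later therapy counting as a subsequent treatment.
4. Reconcile that rule with the wording on the most invasive treatment, and say which date ends the interval when another treatment had already started.

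Items 1, 3 and 4 are changes of definition that use the treatment types and dates already listed for collection. The cost is a somewhat smaller sample for the treatment-start interval: if 10% to 25% of the 1064 men chose surveillance (an assumption), about 958 to 798 would remain (1064 × 0.90 and 1064 × 0.75). The restricted result also applies only to men who went on to active treatment. The planned analysis of treatment choice covers the other part of the question and should be read beside it.
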